**Methods:**

In a cluster randomised controlled trial (RCT) a multifaceted implementation of the PA will be compared with a minimal implementation strategy of the PA. Participating organisations are a university medical centre, a university and a steel factory. Randomisation will take place at department level. Intervention departments will receive a multifaceted implementation strategy of the PA, which incorporates a working group, supervisor training, and supervisor coaching. Control departments will receive the minimal implementation strategy of the PA, consisting of written information only. The primary outcome measure is self-efficacy of supervisors in joint problem solving to improve work functioning of employees with health complaints and to prevent sick leave. A secondary outcome measure at supervisor level is self-efficacy in communicating with employees about situations of reduced work functioning or being at risk for sick leave. Secondary outcome measures at employee level are attitude, self-efficacy, and social influence, with regard to addressing situations of reduced work functioning or being at risk for sick leave, as well as work functioning, psychological well being, and sick leave. Measurements will take place at baseline, and after six and twelve months follow-up. A process evaluation will be performed as well.

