## Background

Sick leave is still a major burden for societies in the Netherlands and other western industrialised countries [1-4]. Besides personal suffering, sick leave also entails extra efforts and costs for organisations and their employees. Human resources (HR) or occupational health services have to take care of sick-listed employees; work remains to be done; colleagues have to take over work; and supervisors may have to support their sick-listed employees. In the Netherlands, the average absence rate was 4.2 percent in 2011, which means a loss of 9 working days per employee per year [3,5]. In addition, direct costs of sick leave for Dutch society in 2010 are estimated at more than €12 billion [2]. By comparison, sick leave costs in the UK in 2013 are estimated at ₤29 billion and in Australia in 2010 at A$30 billion [1,3,4]. This burden of sick leave underlines the urgent need to prevent sick leave.

An effective workplace intervention for organisations to shorten sick leave episodes is the Participatory Approach (PA) [6-9]. PA is a stepwise workplace intervention protocol for supervisors and employees to identify and jointly solve barriers for return to work (RTW). A study by Lambeek et al. demonstrated that an intervention programme with PA for employees sick-listed due to low back pain resulted in a decrease of 120 days to sustainable RTW [8]. Another study also reported that PA is effective for sustainable RTW for employees sick-listed due to distress, if they had the intention to return to work despite symptoms [9]. Although PA is proven to be an effective intervention, it is still not common practice in Dutch organisations [10]. Therefore, an effective strategy for the implementation of PA within organisations may need more research.

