Because of these barriers at different levels, implementation of the PA requires a multifaceted strategy. Shaw et al. showed that working groups combined with training and coaching of supervisors is effective in the prevention of sick leave [17]. This study showed an increase of supervisors’ self-efficacy in their communication with employees with health complaints, a 47% decrease of sick leave episodes, and an 18% decrease of sick leave duration. In general, previous research on implementation of interventions within organisations showed that a multifaceted strategy has proved to be more effective than a single strategy [18]. Moreover, to realise changes within organisations, comprehensive strategies targeted at all different organisational levels are needed [18].

Consequently, the implementation strategy of this study incorporates three components: (1) a working group with representatives of managers, supervisors, employees, HR professionals, and OHPs, (2) supervisor training in PA by in-company OHPs, and (3) coaching of supervisors in PA by in-company OHPs. The main objective of this study is to evaluate the effectiveness of the multifaceted implementation strategy of the PA to increase supervisors’ self-efficacy in joint problem solving for the improvement of work functioning of employees with health complaints, and for the prevention of sick leave. Secondary objectives are: (1) to evaluate the effectiveness of this strategy to improve experienced support and work functioning of employees, (2) to prevent sick leave, and (3) to asses facilitators and barriers for the multifaceted implementation strategy of the PA at all organisational levels.

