#### Sick leave

Sick leave frequency and duration (in calendar days) of employees per supervisor, from six months before baseline up to twelve months follow-up, will be measured with both self-reported and objective data. At all measurements, employees will be asked to report sick leave frequency and duration(s) within the last six months. Sick leave data will also be derived from databases of HR and contracted occupational health services.

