### Statistical analyses

Outcome measures will be compared between both groups at baseline, six, and twelve months follow-up. Primary analyses will be performed at supervisor level and secondary analyses at supervisor and employee level. To assess the success of randomisation, descriptive statistics will be used comparing the baseline measurements of the two groups. In case of unsuccessful randomisation, there will be adjustments for baseline differences. The primary independent variable in the analyses will be binominal representing the allocation to either the intervention or control group. The primary dependent variable is self-efficacy of supervisors in joint problem solving to improve work functioning of employees with health complaints. Changes in primary and secondary outcome variables between baseline and follow-up measurements will be compared between the two groups using linear mixed models at supervisor and employee level. All statistical analyses will be performed according to the intention-to-treat principle and, in case of compliance differences of supervisors, per protocol analyses will be performed as well.

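### Sick leave is to be analysed as change from baseline on an additive scale; baseline as a covariate and a ratio scale would serve this secondary outcome more precisely

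*Protocol article*

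**What the plan says.** All references are to the protocol article.

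- **Statistical analyses** applies one method to every outcome: "Changes in primary and secondary outcome variables between baseline and follow-up measurements will be compared between the two groups using linear mixed models". This holds for supervisors and employees alike. Baseline differences are adjusted for only if the descriptive comparison of the arms suggests that randomisation did not succeed. No transformation, count model or other exception is named for sick leave.
- **Sick leave** (under Outcome measures) defines the variables as "Sick leave frequency and duration (in calendar days) of employees per supervisor, from six months before baseline up to twelve months follow-up". At each measurement "employees will be asked to report sick leave frequency and duration(s) within the last six months".
- The **Methods** part of the abstract lists sick leave among the employee-level secondary outcomes: "as well as work functioning, psychological well being, and sick leave".
- **Background** gives the second of the secondary objectives as "2) to prevent sick leave". The only figure for the level of sick leave is a national absence rate of 4.2 percent, "which means a loss of 9 working days per employee per year". No standard deviation, share of employees without absence, or between-period correlation is given.

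**The concern.** The rule has two weaknesses for this outcome.

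First, subtracting baseline is efficient only when baseline and follow-up correlate strongly. Whether an employee was absent in one half-year is likely to say little about the next half-year, especially for days, where a single long absence can dominate. Subtracting such a baseline adds noise. Entering it as a covariate removes whatever noise it can explain. The article itself treats past sick leave as prognostic, since departments are matched on sick leave frequency before randomisation.

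Second, episodes in six months are small counts, and days are zero unless there was an episode. An additive Gaussian effect is a poor summary of such data. The Background section itself describes earlier sick leave effects as percentage reductions (47% fewer episodes, 18% shorter duration).

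At stake is precision on a stated secondary objective. The pre-baseline window is already being collected, so the better analysis needs no new data.

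**Working it through.** **Plan's own figure.** None exists for sick leave. The stated total of 107 supervisors concerns self-efficacy only. It follows from 34 per arm (difference 0.602, SD 0.88, two-sided 0.05, power 0.80) if there are 6 supervisors per department: 68 × (1 + 5 × 0.05) / 0.80 = 106.25, rounded up to 107. The 6 is back-solved, not stated. It is used below only to set a plausible layout.

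**Step 1: variance of a change score.** With equal variance σ² in both windows and correlation r:

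- change score: 2σ²(1 − r)
- baseline as covariate: σ²(1 − r²)
- ratio: 2/(1 + r)

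Assumed r (the article gives none) and resulting ratio:

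| r | 2/(1 + r) |
|---|---|
| 0.10 (days) | 1.82 |
| 0.20 (days) | 1.67 |
| 0.35 (episodes) | 1.48 |

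Below r = 0.5, the change score is also noisier than follow-up alone, because 2(1 − r) exceeds 1.

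**Step 2: simulated power.** Assumed: 18 departments × 6 supervisors × 10 employees; overdispersed Poisson episodes with mean 0.55 per six months; lognormal episode length with log-SD 1.0 or 1.5, capped at 182 days; true rate ratio 0.75; two-sided 0.05; 300 runs per setting. About 63% of employees had no sick leave in six months. Skewness was about 2.3 for episodes and 4.3 to 5.7 for days. The correlation between baseline and follow-up was about 0.35 for episodes and 0.1 to 0.2 for days.

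| Analysis | Days, log-SD 1.0 | Days, log-SD 1.5 | Frequency, log-SD 1.0 | Frequency, log-SD 1.5 |
|---|---|---|---|---|
| Linear mixed model on change | 28.7% | 15.0% | 64.3% | 60.3% |
| Linear mixed model, baseline-adjusted | 45.0% | 31.3% | 72.0% | 72.0% |
| Negative binomial (GEE), baseline-adjusted | 46.7% | 29.7% | 66.3% | 65.3% |

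The Monte Carlo standard error is at most √(0.25/300) = 2.9 points, so the 2 to 5 point gap between the change analysis and the negative binomial for frequency is small. At a rate ratio of 1, rejection was 1.3% to 5.0% for all three analyses.

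**Step 3: cross-check on department means** (2,000 runs). The simulated mean was 6.16 calendar days per six months. That is 6.16 × 2 × 5/7 = 8.8 working days a year on a five-day week, close to the article's 9. The SD was 18.34, about 3 times the mean.

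| Rate ratio, data used | Outcome | Change | Linear, baseline-adjusted | Log-rate, baseline-adjusted |
|---|---|---|---|---|
| 0.75, 6 + 12 months | Days | 20.1% | 34.1% | 34.6% |
| 0.75, 6 + 12 months | Frequency | 65.4% | 74.1% | 79.3% |
| 0.75, 12 months only | Days | 16.4% | 24.2% | 23.6% |
| 0.75, 12 months only | Frequency | 53.5% | 59.3% | 62.3% |
| 0.82, 6 + 12 months | Days | 11.6% | 17.8% | 19.9% |
| 0.82, 6 + 12 months | Frequency | 39.3% | 42.6% | 49.2% |

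At a rate ratio of 1, rejection was 4% to 6%.

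**Reading.** In both sets of simulations, most of the gain for days appears as soon as baseline becomes a covariate, even in a linear model. Step 1 is an employee-level formula with equal variances. It explains the direction and rough size of the loss, and need not match the clustered simulations exactly.

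**The case against.** **The linear model is not the main culprit.** This stands. With baseline adjustment, the linear mixed model matched the negative binomial for days (31–45% against 30–47%) and did better for frequency (72% against 65–66%). A reader might infer that normal-theory modelling of counts is what wastes power, but the figures point to the change score. The case for a log link rests on scale and fit.

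**Validity is not at risk.** This stands. It is tempting to say that confidence intervals would be unreliable with few clusters. The article does not give the number of departments, and the simulations showed no excess of false positives.

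**The noise is not doubled.** This stands. Relative to follow-up alone, the variance factor 2(1 − r) is 1.3 at r = 0.35 and 1.6 to 1.8 at r = 0.2 to 0.1. It reaches 2 only at r = 0.

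**The wording may mean a repeated-measures model.** This stands only in part. With baseline means left free in each arm, such a model gives essentially the same change contrast. Constraining them to be equal would recover the precision, but the article does not say this and makes baseline adjustment conditional.

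**Sick leave may be summarised per supervisor.** "Sick leave frequency and duration (in calendar days) of employees per supervisor" allows that reading. With 10 employees each, zeros fall to 1–2% and skewness to about 0.9–1.7, so the misfit is much milder. The abstract, however, lists sick leave as an employee-level outcome.

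**Two data sources.** Sick leave "will be measured with both self-reported and objective data". A reader might call the lack of a ranking a defect. The article does not give the two sources equal standing; it only lists them. The choice of main source can be left to the full plan, so it is not part of this point.

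**Conclusion.** The point holds as a minor improvement to a secondary outcome. The article states the method, so this is not a gap that an unseen analysis plan would fill. For sick leave, the change-score rule costs precision: about 1.5 to 1.8 times the variance of a baseline-adjusted analysis at r of 0.35 down to 0.1. In the simulated settings, power for days was about 15–29% instead of 30–47%, and for frequency about 60–64% instead of 65–72%. The additive scale is also ill-suited to zero-heavy, skewed employee-level data.

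The correlations, share of zeros, skewness, cluster layout and rate ratio of 0.75 are all assumptions; the article supplies only a national mean. The algebra in Step 1 depends on r and equal variances, not on the shape of the distribution. Power for days stayed below 50% under every analysis tried, so the change helps without making the trial well powered for days. Nothing here supports a claim of inflated type I error or of harm to the primary analysis of supervisor self-efficacy.

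**What to change.** Add an exception for sick leave to the Statistical analyses section:

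1. Always include the pre-baseline six-month value as a covariate (for example on a log(1 + x) scale), whether or not the arms look balanced, and do not analyse change.
2. Frequency: negative binomial mixed model with log link, a department random effect and an offset for observed time; report a rate ratio.
3. Calendar days: log-link mixed model with the same terms, or a two-part mixed model (any absence; days given absence). If the two-part model is chosen, also report the overall ratio of mean days, because employees with an absence are not a randomised comparison.
4. State that the unit of analysis is the employee. If totals per supervisor are meant, say so; baseline as covariate is still preferable when r is low.

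The cost is wording only, since the pre-baseline window is already collected. Ratios are slightly harder to communicate than a difference in days, and model-based mean days per arm can be shown beside them.

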## Discussion

The present study will evaluate the effectiveness of the multifaceted implementation strategy of the PA, compared with a minimal implementation strategy of the PA, within three organisations. The multifaceted implementation strategy aims to tackle barriers for implementation of the PA at organisational, supervisor, employee, and OHP levels. Representatives of all stakeholders will be involved in a working group and they should identify specific barriers per organisation for implementation of the PA. The implementation strategy especially aims at the supervisor level, because several studies have demonstrated the influence of supervisors’ behaviour on work functioning and well-being of employees [12-15]. Moreover, qualitative studies report lacking of self efficacy and communication skills of supervisors to support employees with work functioning problems or who are at risk for sick leave as important barriers for implementation of the PA [10,16].

This study is the first that will evaluate the application of PA by supervisors to prevent sick leave. Earlier research showed that PA applied by OHPs is effective in shortening sick leave periods [8,9]. Furthermore, implementation of PA for the primary prevention of sick leave corresponds well to current sick leave policies within Dutch organisations. Applying PA by supervisors for the prevention of sick leave will stimulate efforts of both supervisors and employees in improving work functioning of employees with health complaints. Because in-company OHPs are trained by the research team, knowledge and skills about the application of PA are maintained within each organisation. Accordingly, this train-the-trainer principle enables sustainable implementation of PA within each organisation.

### Methodological considerations

This study has some important strengths. First, a cluster-RCT design will be used to evaluate the effectiveness of the multifaceted implementation strategy. Within implementation studies, RCTs are considered the gold standard in investigating the effectiveness of an intervention untainted by bias [7,19]. In contrast to other study designs, an RCT design will control for a priori differences (e.g. willingness of supervisors to participate) and unforeseen factors such as organisational changes, financial problems, and external influences. Second, by cluster randomisation of supervisors at department level, contamination of participating supervisors should be limited as much as possible. By assigning supervisors and their employees per department to either the intervention or the control group will make it less likely that participants of both groups will come into contact with each other.

A third strength of this study is that the PA will be implemented within three different types of organisations; hence, the generalisability of the study results is expected to be good. Supervisors and their employees will be recruited from departments of a steel factory, a university medical centre, and a university. Therefore, the total population of supervisors and their employees will include various types of jobs and professions. Although sick leave causes are expected to differ within these three organisations, supervisors will be able to apply PA for employees with work functioning problems or who are at risk for sick leave, independently of the health related cause. PA can be applied for all types of health complaints, as the intervention focuses on improving work functioning despite health complaints [8,9].

There are also some limitations. First, recruitment bias may influence results at both supervisor and employee level. Because participation of the supervisor is voluntary, participating supervisors may already be more supportive or interested in supporting employees at risk for sick leave, which could lead to ceiling effects. Supervisors who are not motivated to support employees at risk for sick leave may also be less skilled in supporting. Accordingly, employees who have a bad working relationship with their supervisor or do not want to discuss reduced work functioning due to health complaints will probably be underrepresented. Second, inherent in the multifaceted implementation strategy, it will be impossible to blind researchers, in-company professionals, managers and supervisors for the allocated implementation strategy. In addition, because working groups will take place at organisational level, it is possible that control departments have some benefit from working group results.

Third, data of most outcome measures of this study is self-reported and may be influenced by information or recall bias. For example, it is reasonable that supervisors of the intervention departments will fill out questionnaires at follow-up more accurately than those of the control group. Training and coaching of supervisors will probably create more awareness for questionnaire topics and items. In addition, supervisors in the control group will perhaps be less motivated to fill out questionnaires at follow-up after being allocated to the control group.

### Relevance/impact of results

This study will be relevant for all organisations with employees at risk for sick leave in health care, education, and industry. PA is an effective workplace intervention to shorten sick leave periods. However, how to implement this intervention within an organisation effectively, and whether PA is also effective for the prevention of sick leave is still unclear. This study will give insight into the effectiveness of the multifaceted implementation strategy of the PA for supervisors, within three different types of organisations, to increase supervisors’ self-efficacy in supporting employees at risk for sick leave. Results of the study will become available in 2014.
